## Abstract

**Background:**

Lumbar spinal stenosis is the most frequent reason for spinal surgery in elderly people. For patients with moderate or severe symptoms different conservative and surgical treatment modalities are recommended, but knowledge about the effectiveness, in particular of the conservative treatments, is scarce. There is some evidence that surgery improves outcome in about two thirds of the patients. The aims of this study are to derive and validate a prognostic prediction aid to estimate the probability of clinically relevant improvement after surgery and to gain more knowledge about the future course of patients treated by conservative treatment modalities.

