### Study sample size

Sample size is calculated for objective one, the development of a prognostic function for patients undergoing spine surgery, one year after surgery. Outcome after surgery will be quantified by the Swiss Spinal Stenosis Questionnaire (SSM)[28] and results will be dichotomized. An improvement of more than 0.5 points on the symptom severity scale and physical function scale in the SSM will be categorized as improved. According to the original publication [28] 0.5 points represents a clinically relevant improvement for the patients (Minimal Clinical Important Difference). We estimate that 60% of all patients with verified diagnosis will undergo surgery and two thirds of these (between 60% and 70%) of patients will show an improvement of more than 0.5 points in both scales (symptom severity and physical function) one year after surgery. To estimate the effect of ten prognostic variables we need roughly 100 patients without improvement, as defined above, after surgery. This leads us to include 350 patients in the study who undergo surgery.

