### Statistical analysis

Epidemiologic data and patients' descriptive data available on continuous scales will be presented with medians, interquartile ranges or means and standard deviations as appropriate. Categorical data will be presented as rates and percentages. Associations of the continuous independent variables with the outcome variables will be reported using simple logistic regressions. Results from univariate analysis will guide multivariable modeling.

Assessment of associations will be performed using multi-variable models including potential confounders along with the independent variables of interest. Prognostic scores will be built using either logistic regression analysis or Cox proportional hazard models. Models will be validated in subsamples by cross validation. Calibration and discrimination of the cross-validated prognostic instruments will be assessed using the Brier Score.

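### The Brier score alone is assigned to measure both calibration and discrimination; undecomposed it shows neither, so the overfitting to be expected here would not be visible

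*Protocol article*

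**What the plan says.** The Abstract (Background) gives the aim as to "derive and validate a prognostic prediction aid to estimate the probability of clinically relevant improvement after surgery". Under Statistical analysis the article says "Prognostic scores will be built using either logistic regression analysis or Cox proportional hazard models", then "Models will be validated in subsamples by cross validation", and then "Calibration and discrimination of the cross-validated prognostic instruments will be assessed using the Brier Score". Nothing else in the article names a c-statistic, a calibration slope, intercept or plot, or a split of the Brier score into components.

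The setting comes from Study sample size. The article expects that "two thirds of these (between 60% and 70%) of patients will show an improvement of more than 0.5 points in both scales" at one year. It also says "To estimate the effect of ten prognostic variables we need roughly 100 patients without improvement" and "This leads us to include 350 patients in the study who undergo surgery".

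**The concern.** The Brier score is the mean squared difference between predicted probability and observed outcome. It rises with miscalibration, falls as the predictions separate patients better, and also contains the variance of the outcome itself. The article names calibration and discrimination as two properties to be assessed and gives both to this one total.

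This is a stated choice, not detail left to another document. An analysis plan that followed the sentence literally would inherit it. The product of the study is an individual probability, and the Discussion says the results should help patients and physicians decide on therapy. For that use, readers need to know whether patients given 80% improve about 80% of the time, and whether improvers are ranked above non-improvers. The Brier total answers neither question.

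**Working it through.** **Inputs from the article (Study sample size):** 350 operated patients, ten predictors, improvement rate 2/3 (range 60% to 70%). Expected non-improvers are 350 × 1/3 = 117 (350 × 0.40 = 140 to 350 × 0.30 = 105), or about 10 to 14 per predictor. The article states no Brier value or threshold, so there is no figure to reproduce.

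**Assumptions, not in the article:** a logistic model with a normal linear predictor; SD 0.35, 0.5, 0.55 and 1.0, giving true AUC of about 0.60, 0.64, 0.65 and 0.74; 10-fold cross-validation.

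**Formula:** Brier = REL − RES + p(1−p). REL is the mean squared gap between predicted and true risk. RES is the variance of true risk across predictions.

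**Step 1, no-information value.** Predicting 2/3 for everyone has REL = RES = 0, so Brier = 2/3 × 1/3 = 0.222. At 60% improved it is 0.60 × 0.40 = 0.240, and at 70% it is 0.70 × 0.30 = 0.210.

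**Step 2, one score with two explanations.** A perfectly calibrated rule with AUC 0.60 scores 0.216, so RES = 0.222 − 0.216 = 0.006. A rule with true AUC 0.65 would score 0.209 if calibrated, so RES = 0.222 − 0.209 = 0.013. If overfitting adds REL = 0.013 − 0.006 = 0.007, it also scores 0.216. The total cannot say which rule is in hand.

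**Step 3, complete masking.** At SD 0.5 (AUC 0.64), RES = 0.0113 and the calibrated Brier is 0.211. With a calibration slope of 0.46, REL also equals 0.0113, the two cancel, and the score is 0.222. That equals the rule that predicts 2/3 for everyone.

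**Step 4, how much overfitting to expect.** Simulated cross-validation with n = 350 and ten predictors, 200 runs per predictor strength:

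| True AUC | Median cross-validated slope |
|---|---|
| 0.65 (SD 0.55) | about 0.56 |
| 0.74 (SD 1.0) | about 0.78 |

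The mean prediction stayed within 0.6 percentage points of the observed rate in every run.

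**Step 5, what such slopes mean for a patient.** Take the calibration line through the average risk of 2/3 (odds 2), as step 4 supports. A prediction of 80% has odds 4, which is twice the average.
- Slope 0.56: true odds are 2 × 2^0.56 = 2.95, or 75%. For a prediction of 50% (odds 1), true odds are 2 / 2^0.56 = 1.36, or 58%.
- Slope 0.78: the same predictions correspond to 2 × 2^0.78 = 3.43, or 77%, and 2 / 2^0.78 = 1.16, or 54%.

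A calibration slope or plot shows these gaps directly. The Brier total does not.

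**The case against.** **The score does respond to both properties.** It is a proper score and can be decomposed into reliability and resolution, and one sentence in a condensed article does not exclude that. This is fair, and a decomposition would go far towards an answer. But the article names the score, not its components, so the point stands for the score as stated.

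**A reader might infer that a rule with a grossly wrong average could pass.** One can construct a rule with AUC 0.74 and mean prediction 82.5% against a true 66.7% that scores 0.215, much like the calibrated AUC 0.60 rule. The documents do not support this as a practical risk. The score is to be applied to models fitted and tested within one cohort, where a logistic intercept reproduces the observed rate almost by construction (step 4). Slope error is the realistic fault.

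**Complete masking is limited to weak predictors.** At AUC 0.74 the slope would have to fall to 0.35 to match the no-information score. The simulated 95% range there was 0.66 to 0.84, and no run scored worse than the no-information rule. This stands and narrows the point.

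**A reader might infer that the score is too noisy to be of use.** The gain of a calibrated AUC 0.65 rule over no information is 0.013, and the standard error of a single Brier score at n = 350 is about 0.009. That is the wrong comparator, because both rules are scored on the same patients. The paired standard error of the difference is about 0.0056, so the gain is 0.0135 / 0.0056 = 2.4 standard errors.

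**A reader might infer that a poor rule would be accepted, or that raw scores would be compared between the surgical and conservative rules or across years.** The article sets no acceptance threshold and plans no such comparison. The dependence on prevalence in step 1 is a reason to scale the score, not an error in a planned analysis.

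**Conclusion.** The point holds in a limited form. The article assigns calibration and discrimination to one score that, undecomposed, mixes both with the outcome variance and can show neither. At the planned size, cross-validated slopes of about 0.56 to 0.78 are to be expected for true AUCs of 0.65 to 0.74. For predictions of 80% or 50% that means errors of roughly 3 to 8 percentage points, which the Brier total would not reveal.

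The algebra does not depend on predictor strength. The slopes and AUCs do; they also rest on the logistic-normal model, on 10-fold cross-validation and on fitting all ten predictors. Sample size, outcome, data collection and model fitting are untouched, and the missing measures can be computed later from the same predictions. It should be fixed, but it is not a critical fault.

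**What to change.** Replace the sentence on the Brier score under Statistical analysis with separate measures, all computed on the cross-validated predictions:

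- **Discrimination:** the c-statistic (Harrell's C where a Cox model is used) with a 95% confidence interval.
- **Calibration:** the calibration slope and a smoothed calibration plot. Calibration-in-the-large adds almost nothing under internal validation.
- **Overall accuracy:** the Brier score, scaled as 1 − Brier / Brier of the no-predictor model. If its gain over that model is tested, use the paired standard error.

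The cost is a change of wording and a few extra lines of analysis code. No new data, patients or visits are needed.

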## Discussion

This protocol describes the rational, methodology and design of a prospective, multi-center cohort study within hospitals in Zurich including patients with symptomatic lumbar spinal stenosis.

Based on the results of the study we will learn about indicators predicting the future course of patients with lumbar spinal stenosis with and without surgical therapy. These results will support physicians in informing patients, some of them suffering from more than one illness, about the expected course of the illness and help patients and physicians in deciding which therapy to choose.
